#### Process and Mechanism Measures

Weekly and mid-module process measures (eg, alliance, digital engagement, exercise evaluations, and mechanisms related to shame and guilt) will be summarized descriptively and explored in relation to symptom patterns.

#### Qualitative Analysis

Qualitative interviews with adolescents, caregivers, and therapists will be analyzed using reflexive thematic analysis following Braun and Clarke [56,57]. The analysis will primarily adopt an inductive, experiential-semantic approach, focusing on participants’ accounts of feasibility, acceptability, and engagement while allowing for interpretative depth in identifying patterns across participant groups. Reflexivity will be actively integrated, with researchers reflecting on how their clinical and theoretical perspectives may influence the analytic process [56,57]. Given the inclusion of adolescents, caregivers, and therapists, both within-group and cross-group patterns will be explored to identify shared and divergent perspectives.

### Progression Criteria

Progression to a fully powered noninferiority RCT will be determined based on predefined feasibility criteria established a priori, in accordance with CONSORT recommendations for pilot and feasibility studies. The pilot trial will be considered feasible to progress if the following thresholds are met: (1) recruitment: ≥60% of eligible participants enroll; (2) retention: ≥70% of enrolled participants complete the postintervention assessment; (3) acceptability: mean ratings of ≥4/5 from adolescents and caregivers on satisfaction and usability measures; and (4) data completeness: ≥80% of planned data points are collected across core assessment points.

These thresholds are consistent with feasibility patterns observed in comparable interventions. For example, blended trauma-focused cognitive therapy trials have reported high retention (approximately 88%) and strong satisfaction ratings (approximately 4.5/5), as in routine psychiatric care [58]. Similarly, digital PTSD interventions for youth have used recruitment, adherence, and retention as primary feasibility markers, with retention typically ranging from 70% to 90% [59]. Additional digital trauma-focused programs for adolescents and young adults report comparable feasibility patterns [12]. Together, these findings support the feasibility thresholds selected for the present pilot trial.

These criteria will guide decisions regarding whether the intervention and trial procedures are sufficiently feasible and acceptable to proceed to a fully powered trial. If one or more thresholds are not met, the research team will review barriers and determine whether procedural, methodological, or intervention-specific modifications are required before advancing to the next phase.

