The objectives will be (1) to assess the feasibility of delivering bTF-CBT-C in routine care (eg, recruitment, retention, and adherence); (2) to evaluate the acceptability of the intervention (eg, satisfaction ratings and qualitative feedback); and (3) to explore patterns of change in clinical and mechanism-related outcomes, including estimation of variability to inform the design of a fully powered noninferiority trial.

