Adverse events (youth, caregiver + therapist)			✓	✓	✓
Primary outcomes (acceptability)					
Satisfaction (youth + caregiver)				✓	
Therapeutic alliance (youth, caregiver, therapist)^d^			✓	✓	
Digital treatment evaluation (youth + caregiver)^d^			✓		
Exercise evaluation^d^			✓		
Qualitative interviews			✓	✓	✓
Exploratory and clinical outcomes					
PTSD^e^ symptoms (CATS-2^f^, CRIES-13^g^)	✓		✓	✓	✓
Dissociation (DSQ-12^h^)	✓			✓	✓
Self-compassion (CEASY-SE^i^)	✓		✓	✓	✓
Emotion regulation (DERS-16^j^)	✓			✓	✓
Depression/anxiety/suicidality (MADRS-Y^k^, RCADS^l^)	✓		✓	✓	✓
Progression criteria					
Recruitment ≥60%	✓				
Retention ≥70%			✓	✓	✓
Acceptability ≥4/5				✓	
Data completeness ≥80%			✓	✓	✓

a SPIRIT: Standard Protocol Items: Recommendations for Interventional Trials.

b bTF-CBT-C: blended trauma-focused cognitive behavioral therapy with compassion.

c TF-CBT: trauma-focused cognitive behavioral therapy.

d Repeated mechanism/process measures (eg, therapeutic alliance, digital treatment evaluation, exercise evaluation, shame visual analogue scale, Trauma-Related Shame Inventory/Trauma-Related Guilt Inventory) are collected throughout the stabilization and trauma phases. A detailed full schedule table with all weekly/mid-module assessments (T0-T9) is provided in Multimedia Appendix 1.

e PTSD: posttraumatic stress disorder.

f CATS-2: Child and Adolescent Trauma Screen, version 2.

g CRIES-13: Children’s Revised Impact of Event Scale, 13-item version.

h DSQ-12: Dissociative Symptoms Questionnaire, 12-item version.

i CEASY-SE: Compassionate Engagement and Action Scale for Youth – Swedish Version.

j DERS-16: Difficulties in Emotion Regulation Scale, 16-item version.

k MADRS-Y: Montgomery-Åsberg Depression Rating Scale for Youth.

l RCADS: Revised Child Anxiety and Depression Scale.

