### Sample Size

As this is a pilot RCT, the sample size is set at 40 adolescents (20 per arm). This sample size is expected to enable estimation of key feasibility parameters, including recruitment, retention, adherence, and data completeness, as well as estimates of variability in outcome measures [34,35]. The selected sample size also reflects practical considerations related to recruitment within rural child and adolescent psychiatric services [36,37]. No formal power calculation will be conducted, as the trial is not designed to test intervention effectiveness but to inform the design and sample size planning for a future fully powered noninferiority trial.

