### Recruitment and Randomization

Participants will be recruited through child and adolescent psychiatry clinics in the regions of Norrbotten and Västerbotten. Clinicians or research staff will provide information about the study to potentially eligible adolescents and caregivers during routine clinical contacts, after which interested families will be invited to undergo eligibility screening and informed consent.

Following completion of baseline assessments, eligible participants will be randomized in a 1:1 ratio to either bTF-CBT-C or standard TF-CBT. An independent researcher not involved in recruitment or treatment will generate a computer-based randomization sequence using permuted blocks (block size=4) to maintain balance between study arms. Randomization will be stratified by geographic region to account for contextual differences between sites.

Allocation will be concealed using sequentially numbered, sealed, opaque envelopes prepared by the independent researcher. Envelopes will be opened only after baseline assessments are finalized. Due to the nature of psychological treatment, therapists and participants cannot be blinded to group assignment; however, outcome assessors will remain blinded whenever feasible to minimize assessment bias.

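### The 70% retention criterion pools both arms, so it can be met with only 10 of 20 bTF-CBT-C participants assessed at T2, and a pooled pass prompts no review

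*Protocol article*

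**What the plan says.** The protocol article, under Progression Criteria, lists four thresholds (recruitment, retention, acceptability, data completeness) and states "The pilot trial will be considered feasible to progress if the following thresholds are met". The second is "retention: ≥70% of enrolled participants complete the postintervention assessment". Table 1 under Study Design repeats it as "Retention ≥70"% and ticks it at T1, T2 and T3. Neither place names an arm, and no other section sets a retention threshold for one arm or for the gap between arms.

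Under Sample Size, "the sample size is set at 40 adolescents (20 per arm"). Under Recruitment and Randomization, "eligible participants will be randomized in a 1:1 ratio to either bTF-CBT-C or standard TF-CBT". Enrolled participants therefore include both arms.

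The first objective, at the end of the Introduction, is "to assess the feasibility of delivering bTF-CBT-C in routine care (eg, recruitment, retention, and adherence"). Progression Criteria adds that the thresholds help decide "whether the intervention and trial procedures are sufficiently feasible and acceptable to proceed to a fully powered trial". If a threshold is missed, the team reviews barriers; no review is prescribed when all are met.

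**The concern.** The first objective asks whether bTF-CBT-C can be delivered and names retention as an indicator. Under the pooled threshold, half of the retention evidence comes from participants receiving standard in-person TF-CBT. Good T2 completion there can offset poor completion in the experimental arm, and the criterion still reads as met. The pooled count gives the same answer whichever arm is losing participants.

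This matters for the next step. The pilot is meant to prepare a two-arm noninferiority trial, where unequal loss to assessment threatens the comparison. The only prescribed response to poor retention is the barrier review, and that starts only when a threshold is missed.

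**Working it through.** **Inputs from the protocol article.** 20 per arm and 40 in total (Sample Size); 1:1 allocation (Recruitment and Randomization); threshold 70% of enrolled participants at the postintervention assessment, T2 (Progression Criteria). The document gives no expected retention by arm, so the arm-level rates below are assumptions, shown over a range.

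**Step 1: the threshold as a count.** 0.70 × 40 = 28 completers. A 70% threshold within one arm is 0.70 × 20 = 14.

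**Step 2: the fewest bTF-CBT-C completers that meet the pooled threshold** (28 minus control completers).

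| Control completers | bTF-CBT-C needed | bTF-CBT-C not assessed |
|---|---|---|
| 14/20 | 14/20 | 30% |
| 16/20 | 12/20 | 40% |
| 17/20 | 11/20 | 45% |
| 18/20 | 10/20 | 50% |
| 19/20 | 9/20 | 55% |
| 20/20 | 8/20 | 60% |

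For example, 10/20 + 18/20 = 28/40 = 70%, which meets the criterion.

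**Step 3: probability of meeting the criterion.** Let X ~ Bin(20, p_E) be bTF-CBT-C completers and Y ~ Bin(20, p_C) control completers, independent. The pooled rule is P(X + Y ≥ 28), by exact convolution. The arm rule is P(X ≥ 14).

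| p_E | p_C | Pooled rule | bTF-CBT-C arm rule |
|---|---|---|---|
| 0.55 | 0.70 | 0.206 | 0.130 |
| 0.55 | 0.80 | 0.437 | 0.130 |
| 0.55 | 0.85 | 0.579 | 0.130 |
| 0.50 | 0.70 | 0.123 | 0.058 |
| 0.50 | 0.80 | 0.304 | 0.058 |
| 0.50 | 0.85 | 0.433 | 0.058 |
| 0.50 | 0.90 | 0.581 | 0.058 |

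By symmetry, p_E = 0.85 with p_C = 0.55 also gives 0.579 under the pooled rule.

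**Step 4: can data completeness (at least 80% of planned data points) stop these cases?** Assume equal weight per visit, T2 = 70%, and T3 equal to T2.
- Counting T0 to T3: (100 + T1 + 70 + 70)/4 ≥ 80 requires T1 ≥ 80%.
- Counting T1 to T3, as ticked in Table 1: (T1 + 70 + 70)/3 ≥ 80 requires T1 = 100%.

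On the T1 to T3 count, if T1 losses are further assumed to be half of T2 losses, the chance of meeting both retention and completeness falls to 0.18 at 55%/85% and 0.17 at 50%/90%. Completeness can therefore block many of these cases, depending on how it is counted, but it does not rule them out.

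**Step 5: cost of requiring both the pooled and the bTF-CBT-C threshold,** P(X ≥ 14 and X + Y ≥ 28).

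| True retention, both arms | Pooled only | Pooled and bTF-CBT-C |
|---|---|---|
| 0.70 | 0.577 | 0.473 |
| 0.75 | 0.821 | 0.719 |
| 0.80 | 0.957 | 0.895 |

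Wilson 95% intervals: 28/40 gives 55% to 82%; 14/20 gives 48% to 85%.

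**The case against.** Pooled retention is a legitimate target. The criteria judge trial procedures as well as the intervention, and the next trial has two arms, so collapse of the control arm would be a real reason not to proceed. This stands, and it rules out simply moving the threshold to bTF-CBT-C: that would accept 14/20 with control at 6/20.

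Several stronger readings are tempting, but the document does not support them.

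- *That bTF-CBT-C would be declared feasible despite losing half its participants.* Retention is one of four thresholds that must all be met, and completeness can block some of these cases. The 0.58 is not the probability of a go decision.
- *That no criterion looks at the experimental arm.* The usability part of the acceptability criterion in effect does, because the web-based components are described only for bTF-CBT-C. It does not measure retention, and its mean comes from those who respond.
- *That such a gap between arms is expected.* The benchmarks under Progression Criteria are about 88% for blended trials and 70% to 90% for digital ones. The Introduction describes travel and staffing barriers to in-person care. Rates of 50% to 55% for bTF-CBT-C are a stress test, not a forecast. The same benchmarks come from blended and digital programmes, however, so they justify a threshold for the blended arm better than one for a mixture.
- *That participants are lost to treatment.* Retention is completion of the T2 assessment. Adherence is a separate feasibility outcome and is not a progression criterion.

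Finally, a CONSORT flow diagram is planned and the criteria guide the decision, so the team may well see a gap between arms. Nothing obliges it to act on one when the pooled threshold is met.

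**Conclusion.** The point holds for the retention criterion. As written it is met at 28/40 regardless of arm, so 10/20 in bTF-CBT-C passes if control reaches 18/20, and no review follows. The counts rest on the plain reading of enrolled participants as both arms and on full recruitment of 20 per arm.

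The probabilities also rest on assumed arm-level rates and independent binomial outcomes. At 55%/85% the pooled criterion is met with probability 0.58, against 0.13 for the arm threshold. With bTF-CBT-C at 50% it is 0.30 to 0.58 for control at 80% to 90%, against 0.06. The gap narrows as control retention falls: at 50%/70% it is 0.12 against 0.06. The rule should be changed, but the size of the problem depends on a control rate that the document does not state.

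**What to change.** Keep the pooled 70% criterion as the test of trial procedures. Add that retention in the bTF-CBT-C arm must also be at least 70% (14 of 20 at T2), and state that failure of either triggers the existing barrier review. Report retention and data completeness by arm, and the between-arm difference with a 95% CI.

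This changes only the wording of the rule; no new data are needed. With 6 participants enrolled at submission, it can be settled before many T2 results exist.

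There is a statistical cost. The arm-level estimate is less precise, and a feasible intervention passes somewhat less often: the probability falls from 0.96 to 0.90 at 80% in both arms, and from 0.58 to 0.47 at exactly 70%. Because the consequence is a review and not automatic termination, that cost seems acceptable.

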#### Digital Treatment Evaluation

Digital treatment evaluation will assess usability, engagement, and perceived helpfulness of the web-based components. Youth and caregivers will complete an 11-item scale rated on a 5-point Likert scale (0‐4), informed by established usability and technology acceptance frameworks. Higher scores will indicate greater usability, satisfaction, and perceived therapeutic value.

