#### Treatment Satisfaction (Youth)

Treatment satisfaction will be assessed using a structured measure that evaluates perceived helpfulness, quality of the therapeutic relationship, satisfaction with delivery formats (web-based application, video, and in-person), and perceived improvement. Items will be rated on Likert-type scales, with optional free-text responses. Higher scores will represent greater satisfaction.

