### Analysis

#### Quantitative Analysis

All quantitative analyses will follow the intention-to-treat principle [53], including all randomized participants in their assigned condition. Consistent with recommendations for pilot and feasibility trials, analyses will focus on estimating feasibility and acceptability metrics using descriptive statistics (eg, proportions, means, and 95% CIs). These outcomes will be interpreted in relation to predefined progression criteria to inform decisions about trial procedures.

Clinical and process outcomes will be analyzed descriptively, with a focus on estimation and patterns rather than formal hypothesis testing. To support interpretability, these outcomes will be organized into predefined conceptual domains (eg, clinical symptoms, compassion-related processes, and emotion regulation) and interpreted in terms of overall patterns across related measures rather than individual statistical significance.

Exploratory clinical outcomes will be examined to describe symptom trajectories and estimate variability, thereby informing the design of a future, fully powered noninferiority trial. Baseline-adjusted analysis of covariance models and linear mixed effects models will be used descriptively to examine patterns of change over time across study conditions and to generate variance estimates and confidence intervals, rather than to formally test between-group differences. Individual-level changes will be assessed using the Reliable Change Index [54,55]. All analyses will be conducted using standard statistical software (eg, R or SPSS).

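### The acceptability progression threshold of 4/5 does not fit the 0–4 usability scale: read raw it equals the scale maximum, and rescaled it has two different values

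*Protocol article*

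**What the plan says.** The Progression Criteria section lists four thresholds, set in advance, for moving to the full noninferiority trial. The third is "acceptability: mean ratings of ≥4/5 from adolescents and caregivers on satisfaction and usability measures". Table 1 (Study Design) repeats it as "Acceptability ≥4/5", with a single tick at T2. The same section supports its thresholds by pointing to a blended trial with "strong satisfaction ratings (approximately 4.5/5".

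The usability instrument is described under Digital Treatment Evaluation: "Digital treatment evaluation will assess usability, engagement, and perceived helpfulness of the web-based components". On its format the text says "Youth and caregivers will complete an 11-item scale rated on a 5-point Likert scale (0‐4", and on its direction, "Higher scores will indicate greater usability, satisfaction, and perceived therapeutic value". In Table 1 this instrument is ticked at T1. Footnote d to that row says that such measures are repeated over the stabilization and trauma phases, with the detailed schedule in Multimedia Appendix 1.

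For satisfaction, the section Treatment Satisfaction (Youth) says only "Items will be rated on Likert-type scales, with optional free-text responses". No numeric range is given. Table 1 ticks satisfaction at T2.

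**The concern.** A cut-off out of five has been attached to an instrument whose top score is four, and no rule links the two. The threshold and the scale are both printed in the article, so this is a mismatch between two stated facts and not a detail left to another document.

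Acceptability is a primary outcome and one of the four progression thresholds. If 4 is applied to the raw mean, the usability part will be missed even by an application that users rate very highly. If the team converts instead, it must choose a conversion, and the plausible choices give different bars. A choice made once ratings are known weakens the claim that the criterion was fixed beforehand.

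Two related points need stating for the criterion to be usable. Table 1 puts the instrument's tick and the criterion's tick in different columns, and the criterion names no arm although only bTF-CBT-C uses the application.

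**Working it through.** **Inputs**

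- Threshold: mean of at least 4/5 on satisfaction and usability measures (Progression Criteria; Table 1).
- Usability instrument: 11 items, five categories coded 0 to 4, higher is better (Digital Treatment Evaluation).
- Planned size: 40 adolescents, 20 per arm (Sample Size).
- The article's benchmark: a satisfaction rating of about 4.5/5 (Progression Criteria).
- Conversion between 0–4 and a scale out of five: none stated.

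The threshold is a fixed number, not derived from others, so there is no figure of the plan to reproduce. The check is what the number means on the instrument's own scale.

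**Step 1: raw reading.** If every item is at most 4, a mean of at least 4 requires every item from every rater to equal 4. With n raters and 11 items, one item scored 3 gives a mean of 4 − 1/(11n):

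| Raters | Items | Mean with one item at 3 |
|---|---|---|
| 14 (70% of 20) | 154 | 4 − 1/154 = 3.9935 |
| 20 | 220 | 4 − 1/220 = 3.9955 |
| 40 | 440 | 4 − 1/440 = 3.9977 |

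All three miss. If 90% of items are scored 4 and the rest 3, the mean is 0.9 × 4 + 0.1 × 3 = 3.90, also a miss.

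**Step 2: rescaled readings.**

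- Fourth of five categories (1–5 shifted to 0–4): 4 − 1 = 3.0.
- 80% of the maximum: 0.8 × 4 = 3.2.

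The two differ by 0.2, and both lie well below the raw cut-off (by 1.0 and 0.8). An observed mean of 3.1 passes at 3.0, fails at 3.2 and fails at 4.0.

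**Step 3: the article's own benchmark.** A rating of 4.5/5 becomes 4.5 − 1 = 3.5 by the shift, or (4.5/5) × 4 = 3.6 by proportion. Either passes both rescaled cut-offs and misses the raw one. A result as good as the one cited in support of the threshold would therefore not meet it on the raw reading.

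**Step 4: is 0–4 just loose notation for 1–5?** The article writes 1–5 where it means that coding (DERS-16, Parental Stress Scale). Among the acceptability measures, alliance runs 0–6, exercise ratings run −2 to +2, and satisfaction has no printed range. No acceptability instrument has a stated top score of five.

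**Step 5: time point and arm.** Table 1 ticks the Digital Treatment Evaluation at T1 and the criterion at T2. Footnote d describes repeated collection, so several measurements may exist, but nothing in the article says which one is compared with the threshold. The application is part of bTF-CBT-C (Digital Components; Experimental Arm), and standard TF-CBT is delivered in person at the clinic (Control Arm). Usability ratings can therefore come only from bTF-CBT-C. Satisfaction could come from either arm, and the criterion does not say which.

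**The case against.** The strongest reply is that the text says 4/5 and not 4, calls the instrument a five-point scale, and cites a benchmark out of five. A reader would naturally take the fourth of five categories, or 80% of the maximum. This stands in part. It defeats the inference that the usability part can be met only by perfect scores, which holds on the raw reading alone. It does not supply a cut-off, because the two natural conversions disagree and the article chooses neither.

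Three other inferences are tempting and are not supported:

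- **That a miss ends the programme.** If one or more thresholds are missed, the team reviews barriers and decides whether modifications are needed (Progression Criteria, repeated in Results). The consequence is a review, though one that a scaling mismatch could set off.
- **That usability is never measured when the criterion is judged.** Footnote d describes repeated collection, and the full schedule is in an appendix not shown here. What can be said is that the measurement that counts is not named.
- **That the satisfaction mean is biased upward by dropout and contradicts the intention-to-treat statement.** That statement, "including all randomized participants in their assigned condition", concerns analysis by assigned arm, and a mean of available ratings does not contradict it. No document says how dropouts would rate. As an assumed example, take 70% responding with a mean of 4.2. The overall mean reaches 4 when non-responders average (4 − 0.7 × 4.2)/0.3 = 3.53, so the result turns on a value nobody has. At the article's benchmark retention of about 88%, assumed non-responder means of 2.5 and 3.0 give 0.88 × 4.2 + 0.12 × 2.5 = 3.996 and 0.88 × 4.2 + 0.12 × 3.0 = 4.056, one on each side of the line. Retention also has its own threshold.

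On the arm, it is fair to answer that usability implies bTF-CBT-C and that the second objective concerns acceptability of that intervention. This makes the arm a clarification, not an error.

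**Conclusion.** The usability part of the acceptability criterion does not fit the instrument it governs. On the raw reading it equals the scale maximum and is unattainable in practice. On the rescaled readings it is 3.0 or 3.2, and any observed mean from 3.0 up to just below 3.2 changes verdict with the choice.

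This rests on two readings of the text: that the Digital Treatment Evaluation is the usability measure meant, being the only questionnaire described as assessing usability for its own sake, and that no conversion is fixed elsewhere, since none appears in the article. It does not rest on any assumed response or dropout rate. It does not extend to the satisfaction scale, whose range the article does not print and the full protocol may.

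The practical weight is moderate. A miss leads to review and not to stopping, but the criterion is meant to be settled in advance and at present is not.

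**What to change.** - State the usability cut-off on the instrument's own 0–4 scale. A mean of at least 3.0 is the direct equivalent of 4 on a 1–5 scale. The documents do not force that value, and another would serve if it is justified and fixed now.
- Judge it in the bTF-CBT-C arm, the only arm that uses the application.
- Name which of the repeated Digital Treatment Evaluation measurements counts, and align the acceptability row under the progression criteria in Table 1 with it.
- State that the satisfaction cut-off is also judged in the bTF-CBT-C arm, on that instrument's own stated range.

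Optionally, as a supportive summary only, report the share of all randomized bTF-CBT-C participants whose rating meets the cut-off, counting missing ratings as not met. It will look less favourable than the mean of available ratings and should not replace it.

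The cost is a protocol clarification and a corrected table row, with no new data. The timing is good: 6 of 40 participants were enrolled at submission in May 2026, and data collection runs to December 2028, so the cut-off can be fixed before most ratings exist.
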